Through the use of scales, behavioral data, and EEG data, this study aims to investigate whether the three sub-components of executive function in individuals with internet gaming addiction are impaired. Furthermore, it will conduct a one-week focused breathing meditation intervention to explore the effectiveness of concise mindfulness on executive function and its impact on brain function mechanisms. This endeavor will provide more targeted intervention strategies for research into executive function.

1. ***Inclusion and exclusion criteria. [Inclusion criteria define the main body of the study and determine the representativeness of the study population; exclusion criteria define individuals within the study population that may affect the study and determine the homogeneity of the study population]***

Inclusion criteria:

(1) Right-handedness;

(2) Normal vision or corrected-to-normal vision;

(3) Age between 18 and 40 years;

(4) Good mental and physical health (PHQ-9 total score < 20, GAD-7 total score < 11);

(5) Absence of other addictions (e.g., smoking, alcohol, gambling);

(6) For individuals with internet gaming disorder (IGD): Internet Addiction Test (IAT) score ≥ 50, DSM-5 score ≥ 5, gaming history exceeding 2 years, and gaming time of more than 14 hours per week;

(7) For recreational gamers: IAT score < 50, DSM-5 score < 5.

Exclusion criteria:

(1) Individuals with asthma, epilepsy, or a history of mental illness;

(2) Those who have taken steroid medications within the past three months;

(3) Individuals who have practiced meditation, yoga, Tai Chi, or Qi Gong for more than 20 hours in the past year or throughout their lifetime, attended meditation or yoga retreats, or participated in any meditation courses;

(4) Individuals unsuitable for electroencephalogram (EEG) testing due to metal implants, severe head injuries, contact dermatitis, or silicone allergies;

(5) Those with a PHQ-9 total score ≥ 20 or a GAD-7 total score ≥ 11;

(6) Individuals with other addictions (such as smoking, alcohol, or gambling);

(7) Individuals with strong adherence to a particular religious belief that would interfere with their ability to participate in the required meditation exercises;

(8) Individuals currently participating in similar trials or other neurophysiological studies.

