(1) In this study, the intervention period focused on breath meditation lasts for one week and serves as a concise mindfulness behavior training. The study will involve a baseline collection of EEG and other relevant data for all participants, a one-week training on the intervention content, collection of post-intervention EEG and other relevant data, and follow-ups (one week, one month, four months, six months, and one year after data collection post-intervention). During the follow-up phase, participants will undergo multiple mindfulness training sessions. Grouping will occur after the baseline data collection for participants is completed.

(2) The breath meditation training is the primary intervention method employed in this study. The design includes grouping into an experimental group and a control group: the experimental group (breath meditation training) and the control group (relaxation training). The recruited participants are from the same school, and their connections make it challenging to implement the criteria for double-blind randomization.

(3) The randomization process for this trial will utilize the random sequence generator available at random.org.

1. ***Blinding. [Blinding is used in treatment studies and diagnostic trials to reduce the risk of implementation bias and measurement bias. Implementing strict confidentiality measures, such as using placebos or simulating procedures, is an effective blinding method. If blinding is necessary and feasible for your study, describe the methods and procedures for implementing blinding]***

This trial involves group therapy, with participants being students from the same school. Therefore, it is possible that among participants who may know each other or even among those who do not, conversations related to the experimental training they are undergoing may arise. Additionally, maintaining blinding for the researchers is quite challenging, as they can easily be influenced by information related to the experiment during the process. As a result, it is not feasible to meet the double-blind requirements of clinical trials.

1. ***Outcome Measures. [Outcome measures are used to evaluate the results of a study and can include primary, secondary, and safety measures, including adverse events and reactions. Please describe the names of the measures, the methods of measurement, and the time points at which they are assessed]***

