(1) Primary indicators: average daily gaming time (self-reported by participants), Five Facet Mindfulness Questionnaire (FFMQ), Internet Addiction Test (IAT), Game Craving Scale (adapted from QSU-Brief), Adolescent Executive Functioning Scale (EFS-A), Barratt Impulsiveness Scale, State Mindfulness Scale, Game Craving Visual Analogue Scale, behavioral data, and EEG data (from EEG equipment).

(2) Secondary indicators: Self-Rated Sleep Status Scale, Depression-Anxiety-Stress Scale (DASS-21), Positive and Negative Affect Schedule (PANAS).

(3) Safety indicators: Researchers will inquire daily during the intervention period whether participants experience any adverse reactions. If there are any adverse reactions, they will communicate in person or by phone with the research staff.

Measurement time points are detailed in item 5.

1. ***Definition of Participant Effectiveness Determination. [This includes definitions for participant withdrawal, exclusion, loss to follow-up, confounding factors, study discontinuation, and study suspension]***

(1) Participant Withdrawal: Each participant can withdraw from the study at any time during the experiment without providing any reason. Participants who withdraw voluntarily will not be included in the analysis. Under the conditions of a mixed study, we have a complete access procedure for withdrawn participants. If participants are willing to provide a reason for their withdrawal, it will be recorded by the researchers.

(2) Participant Exclusion: If participants cannot consistently participate in the group interventions during the training process—where the focused breathing meditation training lasts one week—those who attend fewer than 5 sessions will be considered not fully intervened and should theoretically be excluded or adjusted using a mixed-effects model.

(3) Participant Loss to Follow-up: If any participant cannot be contacted for two consecutive attempts after the intervention is completed, they will be classified as lost to follow-up.

(4) Participant Contamination: After the intervention is completed, we will conduct a census of participants. If any participant in the control group attempts to learn about the training methods of the intervention group (or vice versa) and tries to train, they will be classified as contaminated participants.

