| **Table 1. Evaluated variables**   \| **Variables** \| \| **Measures** \| **Timepoints** \| \| --- \| --- \| --- \| --- \| \| **Primary outcome** \| **Trait-, State-mindfulness** \| Five Facet Mindfulness Questionnaire (FFMQ) [[6](#_ENREF_6" \o "Baer, 2006 #537)] \| -T2, -T1; T0, T1, T2, T3, T4, T5 \| \| State Mindfulness Scale [[7](#_ENREF_7" \o "Yu, 2021 #565)] \| \| **Electroencephalographic (EEG) and behavioral data** \| Behavioral and Electroencephalogram (EEG) data \| \| Heart Rate Variability \| \| **Gaming craving-related metrics** \| Average daily gaming time (self-recorded by participant) \| \| Internet Addiction Test (IAT) [[8](#_ENREF_8" \o "Wang, 2019 #706), [9](#_ENREF_9" \o "Young, 1998 #711)] \| \| Gaming Craving Visual Analogue Scale [[10](#_ENREF_10" \o "Ko, 2013 #65)] \| \| Gaming Craving Short Questionnaire (adapted from QSU-Brief) [[11](#_ENREF_11" \o "Cox, 2001 #543)] \| \| **Impulsivity** \| Barratt Impulsiveness Scale [[12](#_ENREF_12" \o "Patton, 1995 #547)] \| \| **Executive function** \| Adolescent Executive Functioning Scale (EFS-A) [[13](#_ENREF_13" \o "Huang, 2014 #707)] \| \| **Secondary outcome** \| **Sleep status** \| Self-Rating Scale of Sleep (SRSS)[[14](#_ENREF_14" \o "Li, 2012 #708)] \| -T2, -T1; T0, T1, T2, T3, T4, T5 \| \| **Affect, Stress** \| Depression Anxiety Stress Scales (DASS-21) [[15](#_ENREF_15" \o "Gong, 2010 #709)] \| \| Positive and Negative Affect Schedule (PANAS) [[16](#_ENREF_16" \o "Watson, 1988 #71)] \| \| **others** \| **Socio-demographic and clinical information** \| Demographics including name, gender, handedness [[17](#_ENREF_17" \o "Edlin, 2015 #541)], gaming history duration, average weekly gaming time, psychiatric diagnosis or history of mental health problems \| -T1 \| \| **Psychological status** \| Patient Health Questionnaire-9 (PHQ-9) [[18](#_ENREF_18" \o "Kroenke, 2001 #73)] \| \| Generalized Anxiety Disorder-7 (GAD-7) [[19](#_ENREF_19" \o "Spitzer, 2006 #544), [20](#_ENREF_20" \o "shan, 2015 #546)] \| \| **Presence of IGD** \| Diagnostic and Statistical Manual of Mental Disorders, Fifth Edition (DSM-5) nine diagnostic criteria [[21](#_ENREF_21" \o "Petry, 2014 #76)] \| \| Gaming history, average weekly gaming time \| \| **Personal traits** \| Chinese Big Five Personality Questionnaire [[22](#_ENREF_22" \o "Wang, 2011 #710)], attachment style [[23](#_ENREF_23" \o "Li, 2006 #702)], self-compassion [[24](#_ENREF_24" \o "Kong, 2021 #703)] \| |

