| --- | --- | --- | --- | --- | --- | --- | --- | --- | --- | --- | --- | --- | --- | --- | --- | --- | --- | --- | --- | --- | --- | --- | --- | --- | --- | --- | --- | --- | --- | --- | --- | --- | --- | --- | --- | --- | --- | --- | --- | --- |

1. ***Definition, identification methods, and management systems for adverse events and reactions.***

[name] [[25](#_ENREF_25" \o "Farias, 2020 #701)] systematically describes the adverse events and reactions caused by meditation (meditation adverse events, MAEs) in the text, which we categorize as follows:

**Mental MAEs:** The most common include anxiety and depression, while other relatively common issues include psychotic or delusional symptoms, dissociation or depersonalization, fear or phobia, trauma re-experiencing, and suicidal thoughts and behaviors.

**Physical MAEs:** The most common is bodily tension, followed by pain and gastrointestinal issues. Localized pain often involves the abdomen/stomach and neck. Most physical MAEs are based on patient self-reports; however, some variables also used physiological and biological measurement methods, such as heart rate, blood pressure, skin conductance, and cortisol levels (it is not possible to rule out that these physiological measuring methods might cause side effects).

**Neurological/Cognitive MAEs:** The most common are abnormal cognitive experiences, including thought disorganization, forgetfulness, sensory hypersensitivity, and impaired memory reliability. Some patients also experienced involuntary bodily movements and muscle contractions during meditation.

Based on the types of adverse effects mentioned above, to address adverse events during the intervention process, we have included relevant adverse reaction feedback questions in the weekly follow-up questionnaires. The experimental group will conduct weekly monitoring; after collecting the questionnaires, if an adverse event feedback option is marked "yes," the relevant person in charge from the medical school and psychology department will be responsible for communicating with the subjects, assessing their psychological and physiological conditions, and gauging the subjects' willingness. After a tripartite consensus (medical school, psychology department, and the individual subject), they will decide whether the subjects experiencing adverse events can participate in subsequent research.

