1. ***Plan for Sharing Raw Data. [Describe the plan for sharing raw data with the public. Specify the maximum time frame for sharing data, which should not exceed 6 months after the end of the trial. Explain the public platform that will be used for data sharing]***

The raw data will be uploaded to the ResMan Clinical Trial Public Management Platform, http://www.medresman.org.cn.

1. ***Treatment and Management of Participants after the Trial Ends. [Describe how participants who have not experienced improvement in their condition at the end of the trial will continue to receive medical care. Explain the measures that will be taken to ensure their ongoing treatment and management]***

Since the participants included in this study are all healthy university students and are guided by professional instructors in focused breathing meditation training, this training aims to explore the effects of a brief mindfulness intervention on executive function. Additionally, this process can help participants enhance their ability to self-regulate emotions when facing various stressors in real life. If, after the experiment, it is found that any participant's stress level reaches a clinically significant threshold, a psychological counselor from the university's psychological center will provide active intervention and, if necessary, refer them to nearby specialized hospitals for further support.

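### The only score-based care trigger after entry acts after the trial, on stress alone and without a cut-off, although DASS-21 is collected throughout; weekly harm monitoring is assigned to one arm

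*Protocol*

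**What the plan says.** **Scores at entry.** Exclusion criterion (5) in the Protocol's Inclusion and exclusion criteria removes "Those with a PHQ-9 total score ≥ 20 or a GAD-7 total score ≥ 11". Table 1 lists both scales at -T1 only, and neither is among the observation items in the section on baseline measures and observed variables.

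**Scores after entry.** Table 1 schedules "Depression Anxiety Stress Scales (DASS-21") at -T2, -T1 and T0 to T5. Outcome Measures classes it as a secondary indicator, not a safety indicator. No cut-off, reviewer or action is attached to it.

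**Expected harms.** On mental adverse events of meditation, the section on adverse events and reactions says: "The most common include anxiety and depression, while other relatively common issues include psychotic or delusional symptoms".

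**In-trial safety routes.** Outcome Measures (3) states: "Researchers will inquire daily during the intervention period whether participants experience any adverse reactions". Other sections make an adverse event grounds for termination, with clinical care offered. They also put adverse-reaction questions in weekly questionnaires, stop EEG collection on adverse emotions, and give an Emergency Team the duty to identify and intervene. On the weekly questionnaires, the protocol adds: "The experimental group will conduct weekly monitoring".

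**Care after the trial.** The section Treatment and Management of Participants after the Trial Ends offers counselor support and, if needed, referral under this condition: "If, after the experiment, it is found that any participant's stress level reaches a clinically significant threshold".

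**The concern.** The plan acts on a mental-health score when it decides who may enter, and again once the experiment is over. In between it holds repeated depression, anxiety and stress scores and does nothing with them. A participant who scores high but reports nothing, and whom nobody notices, has no stated response while the trial runs. The one rule that does act on a level leaves out the two harms that the protocol lists first, and without a cut-off staff cannot apply it consistently.

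The second strand is even-handedness. If staff monitor weekly for adverse events in one arm only, that arm will tend to yield more recorded events whatever the true rates are. Any comparison of harms between meditation and relaxation would then be biased.

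**Working it through.** The protocol states no figure to reproduce here. The check is a comparison of its sections, plus simple timing.

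**1. Which DASS-21 timepoints carry a rule?** Table 1 gives 2 baseline timepoints (-T2, -T1) and 6 after allocation (T0 to T5), so 2 + 6 = 8. Timepoints with a stated threshold or response: 0 of 8.

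**2. Is another depression or anxiety scale in use after entry?** PHQ-9 and GAD-7 stop at -T1. Entry requires PHQ-9 < 20 and GAD-7 < 11, so whole-number scores up to 19 and 10 are admitted. A participant can therefore start one point below either limit. From then on, DASS-21 is the only scale in Table 1 that names depression and anxiety.

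**3. What starts each route to care?**
- Daily inquiry (Outcome Measures): a reported adverse reaction, in the intervention period only.
- Termination rule (Definition of Participant Effectiveness Determination): an adverse event.
- Weekly questionnaire (section on adverse events): an adverse-event option marked yes.
- EEG stop (same section): a visible rejection response or adverse emotion.
- Emergency Team (Participant management system): an identified adverse reaction, or self-referral.
- Post-trial rule: a stress level, after the experiment.

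Only the last is of threshold type. It has no number and does not mention depression or anxiety.

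**4. How long could a recorded high score wait?** The Fig 2 note places T1 to T5 at 1 week and 1, 4, 6 and 12 months. Taking the experiment to end at the participant's own T5, wait = 12 − visit time in months:
- T0: 12 − 0 = 12
- T1: 12 − 0.25 = about 11.75
- T2: 12 − 1 = 11
- T3: 12 − 4 = 8
- T4: 12 − 6 = 6
- T5: 12 − 12 = 0

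These are the longest waits on that definition, and they apply only if every event-based route misses the participant.

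**5. Who is monitored weekly?** The section on randomization, item (2), defines the groups: "the experimental group (breath meditation training) and the control group (relaxation training"). Put beside "The experimental group will conduct weekly monitoring", the weekly monitoring falls on the meditation arm. The daily inquiry carries no arm limit but ends with the intervention week. After that week, the only active adverse-event inquiry described is the weekly one. The SPIRIT schedule has no row for the weekly questionnaire, so it does not show which arm receives it.

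**The case against.** The best answer is that safety during the trial is layered. There is daily inquiry, termination with care, assessment by medical-school and psychology staff, EEG stopping, and an Emergency Team whose duty has no arm or time limit and is not confined to self-report. Anxiety and depression are named as adverse events, so a participant who reports them is covered. All of this stands. A reader might infer that participants have no protection before the trial ends, and the protocol does not support that. What remains is narrower: nobody is told to look at the DASS-21 scores, and no score calls for action.

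It can also be said that DASS-21 is an outcome and was never promised as a safety tool, so nothing is contradicted. That is fair, and it limits the weight. The instrument behind the post-trial rule can be inferred too: DASS-21 is the only listed scale with stress in its name. The cut-off cannot be inferred.

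On weekly monitoring, the wording could be meant to describe the staff who run the experiment, and the weekly questionnaires themselves carry no arm limit. That reading is possible, but the only definition the protocol gives for the experimental group is the meditation arm. The statistical section plans no between-arm comparison of adverse events, so the bias would reach only such a comparison if one were made.

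Two further inferences should be resisted. The randomization section says "During the follow-up phase, participants will undergo multiple mindfulness training sessions", which might suggest that both arms keep training during follow-up. The Fig 3 caption says that controls have no further practice or intervention after training, so continuing exposure can be argued for the meditation arm only. A reader might also suppose that anonymization makes a high score untraceable. The protocol anonymizes before statistical processing, not at collection, and it keeps the source data, so this does not follow.

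**Conclusion.** The point holds as a gap of minor to moderate weight. After entry, the only threshold-type trigger for care comes after the experiment, covers stress alone and has no cut-off, while depression, anxiety and stress scores are in hand at six post-allocation visits. The longest wait is about 12 months. This assumes that the experiment ends at the participant's T5 and that no event-based route acts first. The protocol gives no basis for estimating how many participants would be affected, so no number is offered.

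The unequal weekly inquiry holds on the protocol's own definition of the experimental group. It would fall away if the sponsor confirms that the phrase means the research team and that both arms are asked. Referral for care is a participant-safety procedure and belongs in the protocol, so a separate statistical analysis plan would not be expected to supply it.

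**What to change.** 1. Score DASS-21 promptly at each visit T0 to T5 in both arms. Refer any depression, anxiety or stress score at or above a cut-off set in advance to the existing Emergency Team and university counselor. The instrument's published severe band is one candidate; the sponsor must choose the values and write them in, since the protocol gives none.
2. In Treatment and Management of Participants after the Trial Ends, name DASS-21, extend the trigger from stress to all three subscales, and make it apply during the trial as well as after it.
3. In the section on adverse events and reactions, state that the weekly adverse-reaction questions and their follow-up apply to both arms.
4. Record any support given, by arm and date, as a co-intervention.

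**Cost.** The questionnaire is already collected and the team already exists, so the work is prompt scoring, amended text, weekly questions to controls if they are not now asked, and some referrals of unknown number. The real downside is that support triggered by a score may alter later DASS-21 values, a secondary outcome. Item 4 is there so that this can be considered when those results are interpreted.
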